### Subject Compensation

#### Costs and Payment

There are no costs to participate in the study. There will be no payment for participation in this study.

### Adverse Event Reporting

There are no potential adverse events for participation in this study.

## Results

Preliminary data analysis for the year 2017 has been completed. Compared to a baseline 2016 survival rate of 47.0%, from 2017 to 2018, CS survival rates were increased to 57.9% (81/140) and 81.3% (26/32), respectively (*P*=.01 for both). Survival in acute MI with CS increased from 52.6% (30/57) to 75.0% (12/16) and in acute decompensated HF from 61.4% (51/83) to 87.5% (14/16). For 2017, CS threshold markers at 12 hours (lactate<3.0 mg/dL, CPO>.6 W, PAPi>1.0) overall survival was 80% (72/90), 93.6% (73/78) and 74% (71/96), respectively. For 2018, CS threshold markers at 12 hours (lactate<3.0 mg/dL, CPO>.6 W, PAPi>1.0), overall survival was 92.3% (24/36), 92% (23/25) and 85.2% (23/27), respectively. Use of RHC was associated with 14% greater survival. Decreases of 5 and 10 hours in the time to implement MCS were associated with increased survival 53.6% and 135.8%, respectively. Age was associated with survival; patient’s ≥75 years old had higher risk of death (odds ratio 3.43, 95% CI 1.20-9.78).

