The implementation and utilization of a designated CS at the IHVI is an effective strategy to mitigate the consequences of cardiogenic shock. The IHVI CS team, founded in 2017, is mobilized for and directed to five goals: (1) the rapid identification of shock through early activation of the CS team and rapid collaborative decision making, (2) early right heart catheterization to facilitate invasive hemodynamic therapy tailored to the patients’ unique presentation, (3) the accelerated initiation of mechanical circulatory support, (4) minimization of vasopressor and inotropic support, and (5) meaningful recovery and survival of the patient [13]. Bi-weekly action and outcomes review are employed to track efficient methodology with the intention of eradicating significant preventable morbidity and death from CS [13]. Utilizing the best and most recent evidence and best practices, a comprehensive care pathway was developed. A six-month training process was focused on individual and team management of the aforementioned five goals, training and rehearsals were implemented to ensure the seamless execution of the adopted algorithms [13]. Prior to implementation of the Cardiogenic Shock team at the IHVI, 30-day survival was approximately 47%, assuming an alpha level of 0.5, two sided. We expect the implementation of an IHVI Shock algorithm to increase 30-day survival by 15%. Thus, 200 subjects in each group provide at least 80% power to detect a statistically significant increase in 30-day survival from 47%.

We propose to study the outcomes associated with CS patients who have been managed by the CS team at the IHVI in order to ascertain the effects on outcome and survival rate. Positive effects in outcomes and survival will indicate a positive correlation between meaningful survival and management by a multidisciplinary shock team. The database compiled from these outcomes will also serve as a clinical archive of distinctive patient characteristics and outcomes to support future evaluation and translational research. The benefit of CS management to patients is a decrease in disability and mortality post CS episode.

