#### Number of Subjects

Our goal is to include approximately 200 patients before and 200 patients after initiation of Shock team. The study group will consist of a retrospective review of all patients receiving Shock Team intervention after diagnosis with acute decompensated heart failure cardiogenic shock, or acute myocardial infarction cardiogenic shock, from January 1, 2017 until Institutional Review Board (IRB) filing of protocol. A second group will consist of current patients receiving shock team intervention.

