### Statistical Considerations and Data Analysis

#### Sample Size

We are estimating 300-400 patients will be included in this analysis. This size is based on prior smaller studies.

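### The plan sets up one pooled before/after contrast, but the preliminary results test 2017 and 2018 separately against a 2016-only rate, with a shared P value that cannot be right for both years

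*Protocol article*

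**What the plan says.** The planning text of the protocol article points to one two-group comparison.

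- **Background and Significance** sizes the study on 30-day survival: "Thus, 200 subjects in each group provide at least 80% power to detect a statistically significant increase in 30-day survival from 47" percent. The expected gain is 15%, and the error rate is printed as "assuming an alpha level of 0.5, two sided".
- **Number of Subjects** repeats the two groups: "Our goal is to include approximately 200 patients before and 200 patients after initiation of Shock team". It then describes a retrospective series of team patients up to IRB filing, and adds: "A second group will consist of current patients receiving shock team intervention".
- **Hypothesis** names the comparator as 2015 and 2016 together.
- **Primary Outcomes** compares current with historical survival. It names no calendar-year contrast.
- **Method of Data Analysis** promises summaries and differences with standard errors and 95% CIs. It names no test.

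The **Results** section departs from this. Against a 2016 rate of 47.0%, without numerator or denominator, it states: "CS survival rates were increased to 57.9% (81/140) and 81.3% (26/32), respectively (*P*=.01 for both"). It gives no pooled team-era figure and no 2015 figure. The **Abstract** prints the same percentages and P value with different counts (58/110 and 81/140), and says that data collection runs to December 31, 2018.

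**The concern.** The comparison that was sized is not the one that was tested. Three things changed between plan and results: the team era was cut by calendar year, the comparator shrank from 2015-2016 to 2016 alone, and each year received its own P value against the same baseline.

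The reader is left with two separate estimates, one of them from 32 patients, and without the pooled estimate that the study was designed to give. The P value attached to both years also needs checking, because two cohorts of such different size and effect are unlikely to share one. Collection was still open, so the deciding contrast could still be fixed before the final analysis. Left unstated, it could be chosen after the yearly results are known.

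**Working it through.** **Inputs.** Baseline 47% and planned gain of 15 points, to 62% (Background and Significance); 200 per group (same section and Number of Subjects); 81/140 and 26/32 (Results). Alpha is printed as 0.5 and is read here as 0.05 two-sided. The 2016 denominator is not given, so 100, 140 and 200 are assumed, with 47, 66 and 94 survivors.

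**1. The plan's own figure.** For two proportions with pooled variance,

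n = [z(0.975)·√(2·p̄·q̄) + z(0.80)·√(p1·q1 + p2·q2)]² / (p2 − p1)².

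With p1 = 0.47, p2 = 0.62 and p̄ = 0.545: [1.960 × 0.7042 + 0.842 × 0.6962]² / 0.15² = 172 per group. At 200 per group, power is Φ[(0.15·√200 − 1.380)/0.6962] = Φ(1.064) = 85.6%. The statement of at least 80% is reproduced, for one contrast. With 200 baseline patients, power for the same 15 points is 78.2% with 140 team patients, 34.7% with 32 and 82.8% with 172.

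**2. Which counts.** The aetiology subgroups in Results add up to its totals: 30/57 + 51/83 = 81/140 for 2017, and 12/16 + 14/16 = 26/32 for 2018. The Abstract's counts do not match its percentages: 58/110 = 52.7%, not 57.9%, and 81/140 = 57.9%, not 81.3%. The Results counts are used here, subject to reconciliation.

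**3. Effect sizes.** These need only the printed 47.0%.

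- 2017: 57.9 − 47.0 = +10.9 points.
- 2018: 81.3 − 47.0 = +34.3 points; Wilson 95% CI for 26/32 is 65% to 91%.
- Pooled: (81 + 26)/(140 + 32) = 107/172 = 62.2%, or +15.2 points.

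The two years also differ from each other (P = 0.014).

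**4. P values with 47% treated as a known constant.** z = (p − 0.47)/√(0.47 × 0.53/n).

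- 2017: 0.1086/0.0422 = 2.57, P = 0.010.
- 2018: 0.3425/0.0882 = 3.88, P = 0.0001.
- Pooled: 0.1521/0.0381 = 4.00, P = 0.00006.

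**5. P values in a two-sample test.** z = (p − p0)/√[p̄·q̄·(1/n0 + 1/n)], uncorrected. For example, 2017 against 94/200 gives 0.1086/0.0551 = 1.97, P = 0.049.

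| Assumed 2016 n | 2017 | 2018 | Pooled |
|---|---|---|---|
| 100 | 0.096 | 0.0007 | 0.015 |
| 140 | 0.073 | 0.0005 | 0.008 |
| 200 | 0.049 | 0.0003 | 0.003 |

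The pooled difference has a 95% CI of 3.0 to 27.4 points with n0 = 100 and 5.2 to 25.2 with n0 = 200.

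**6. Can one baseline give .01 for both years?** For P to round to .01 it must lie between 0.005 and 0.015. For 2018 this needs a baseline of 16 to 29 patients. For 2017 it needs at least 1,194. The ranges do not meet, and with 47% fixed only 2017 gives .01.

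**7. Error rate of an either-year claim.** Two independent tests at 0.05 give 1 − 0.95² = 0.0975. Simulation with a shared baseline, true survival of 47% throughout and 140 and 32 team patients gives 0.0935 (baseline 100) and 0.0950 (baseline 200).

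**The case against.** The best defence is that the plan already implies one contrast. Every planning section describes two groups, before and after. The yearly figures appear only in results labelled preliminary, and an interim display by year does not redefine the analysis. An absent alpha split or decision rule, taken alone, is detail that belongs in an analysis plan. That is accepted: the point rests on what the article did and printed, not on what it left out.

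Three stronger readings are tempting, and the document does not support them.

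- **The two team groups in Number of Subjects are rival tests.** The split falls at IRB filing and fits the retrospective and prospective design. It reads as a data-collection split, and nothing says that the groups will be tested separately.
- **The headline is 81%.** Abstract and Results give both years side by side, and neither the Conclusions nor the Discussion cites 81% or 2018.
- **The contrasts necessarily differ in significance.** With 47% fixed, all three are below 0.05. In a two-sample test 2017 is above 0.05 only if the 2016 baseline has fewer than about 195 patients. The goal of about 200 covers the whole pre-team group, so 2016 alone is probably smaller, but that is an inference.

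Multiplicity also does not overturn the result as printed. The article claims both years, and .01 for each would pass a Bonferroni threshold of 0.025. The 0.095 applies only if either year could carry the claim.

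**Conclusion.** The point holds as a mismatch between the planned contrast and the reported tests. Three parts need no assumption about the baseline size: the sized contrast is not reported, the comparator is 2016 rather than 2015-2016, and the shared P value of .01 cannot be right for both years. The .01 for 2017 matches a test that treats 47% as known, which ignores baseline sampling error and is not the two-group comparison that was sized. On the same basis 2018 would be 0.0001.

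The two-sample P values rest on the assumed 2016 denominator, and all team-era figures rest on the Results counts. The direction of effect is not in doubt: all contrasts favour the team era, and the pooled one stays below 0.05 over the assumed range of 100 to 200. What changes is the estimate offered, 62.2% (+15.2 points) in place of two yearly figures of +10.9 and +34.3, and its evidential basis of 172 patients.

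**What to change.** In Primary Outcomes and Method of Data Analysis, state that the single confirmatory contrast is all eligible team-era patients (January 1, 2017 to December 31, 2018, pooled) against the 2015-2016 controls. Make it a two-sample comparison at two-sided 0.05, performed once at the end of data collection. State that calendar-year figures are descriptive, with CIs and no P values. The sentence must also name one survival endpoint, because the sizing uses 30-day survival and Primary Outcomes uses mortality at hospital discharge.

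In the Abstract and Results:

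- reconcile the conflicting counts;
- give the baseline numerator and denominator;
- remove the P value of .01 shared by the two years;
- show the pooled preliminary estimate (107/172, 62.2% on the Results counts) with its difference from baseline and 95% CI, labelled preliminary.

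The cost is a short addition to the analysis text, one pooled calculation on data in hand and retrieval of the pre-team counts. No new patients are needed.

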**Objective:**

The objectives of this study are (1) to collect retrospective clinical outcomes for acute decompensated heart failure cardiogenic shock and acute myocardial infarction cardiogenic shock, and compare current versus historical survival rates and clinical outcomes; (2) to evaluate Inova Heart and Vascular Institute site specific outcomes before and after initiation of the Cardiogenic Shock team on January 1, 2017; (3) to compare outcomes related to early implementation of mechanical circulatory support and hemodynamic-guided management versus historical controls; (4) to assess survival to discharge rate in patients receiving intervention from the designated shock team and (5) create a clinical archive of Cardiogenic Shock patient characteristics for future analysis and the support of translational research studies.

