**Results:**

Preliminary data analysis for the year 2017 has been completed. Compared to a baseline 2016 survival rate of 47.0%, from 2017 to 2018, CS survival rates were increased to 57.9% (58/110) and 81.3% (81/140), respectively (*P*=.01 for both). Study data will continue to be collected until December 31, 2018.

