### Specific Aims

The specific aims of this study are as follows: (1) to collect retrospective clinical outcomes related to acute decompensated heart failure cardiogenic shock, acute myocardial infarction cardiogenic shock and compare current versus historical survival rates; (2) to collect Inova Heart and Vascular Institute (IHVI) site specific outcomes before and after initiation of the Cardiogenic Shock team on January 1, 2017; (3) outcomes related to implementation of mechanical circulatory support versus no circulatory intervention and type of intervention (ECMO versus intracorporeal axial-flow [Impella]); and (4) to assess survival at 3 time points.

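### The 2018 lactate-marker survival of 92.3% (24/36) is impossible as printed; separately, the six 12-hour marker rates have no comparator, so they show no target effect and do not meet the abstract's third objective

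*Protocol article*

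**What the plan says.** The Results section gives overall survival by year: "CS survival rates were increased to 57.9% (81/140) and 81.3% (26/32), respectively", for 2017 and 2018, against a 2016 baseline of 47.0%. It then reports survival for patients meeting each of three thresholds at 12 hours (lactate, CPO, PAPi, in that order). For 2017, "overall survival was 80% (72/90), 93.6% (73/78) and 74% (71/96), respectively". For 2018, "overall survival was 92.3% (24/36), 92% (23/25) and 85.2% (23/27), respectively". No marker rate is given for patients who missed a threshold or for any year before the team started. The same section reports that right heart catheterization was associated with 14% greater survival, without counts or an interval.

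The third objective in the abstract is "to compare outcomes related to early implementation of mechanical circulatory support and hemodynamic-guided management versus historical controls". The third item under Specific Aims differs and has no hemodynamic-guided element: "outcomes related to implementation of mechanical circulatory support versus no circulatory intervention and type of intervention". The Method of Data Analysis section commits to standard errors and 95% confidence intervals for reported differences. The abstract's Conclusions list hemodynamic-guided management among the parts of a team approach said to be associated with better outcomes than in 2015 and 2016.

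**The concern.** There are two separate problems.

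The first is arithmetic. One of the six marker results contradicts its own percentage and the cohort it comes from. A reader who trusts the fraction takes away about two thirds survival; one who trusts the percentage takes away more than nine in ten.

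The second is what the marker rates can support. A patient can meet a 12-hour threshold only if there is a 12-hour value, which on the natural reading means being alive and measured then. Patients who died earlier stay in the overall denominators of 140 and 32 but cannot be in a marker group. A marker rate above overall survival is therefore expected to some degree even if the marker carries no information. With neither a missed-threshold group nor a pre-team group, that selection cannot be separated from prognosis, nor prognosis from an effect of guided care.

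**Working it through.** **Inputs**, all from the Results section: 2017 overall 81/140, 2018 overall 26/32, and the six marker fractions. The etiology split confirms both totals: 30/57 + 51/83 = 81/140 for 2017 and 12/16 + 14/16 = 26/32 for 2018. Deaths are 140 − 81 = 59 and 32 − 26 = 6.

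**Step 1: reproduce each percentage.**

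| Year, marker | Fraction | Computed | Printed |
|---|---|---|---|
| 2017 lactate | 72/90 | 80.0% | 80% |
| 2017 CPO | 73/78 | 93.6% | 93.6% |
| 2017 PAPi | 71/96 | 74.0% | 74% |
| 2018 lactate | 24/36 | **66.7%** | **92.3%** |
| 2018 CPO | 23/25 | 92.0% | 92% |
| 2018 PAPi | 23/27 | 85.2% | 85.2% |

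Five of the six reproduce, as do 81/140 = 57.9% and 26/32 = 81.3%.

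**Step 2: can 24/36 be reconciled?**
- Percentage: 92.3% of 36 is 33.2. The nearest counts give 33/36 = 91.7% and 34/36 = 94.4%, so no count over 36 gives 92.3%.
- Cohort: 36 > 32.
- Deaths: 36 − 24 = 12 > 6.
- With a numerator of 24, only a denominator of 26 rounds to 92.3%. 24/26 implies 2 deaths among 26 patients, which fits 6 deaths among 32.

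The abstract offers no larger 2018 cohort to rescue the figure. It prints "CS survival rates were increased to 57.9% (58/110) and 81.3% (81/140), respectively", but 58/110 = 52.7% and 81/140 = 57.9%, so neither fraction there matches its percentage.

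**Step 3: what lies outside the 2017 marker groups.** Subtracting each group from 81/140:
- lactate: (81 − 72)/(140 − 90) = 9/50 = 18%
- CPO: (81 − 73)/(140 − 78) = 8/62 = 13%
- PAPi: (81 − 71)/(140 − 96) = 10/44 = 23%

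These remainders mix missed thresholds, deaths before 12 hours and unmeasured patients. They are not not-met rates.

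**Step 4: how far early deaths could move the picture.** The document does not give the number D of 2017 deaths before 12 hours, so D is an assumption. If no such patient is counted at target, the PAPi group bounds it: 96 − 71 = 25 of the 59 deaths were at target, so D is at most 59 − 25 = 34.

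Survival among all patients alive at 12 hours is 81/(140 − D). This runs from 57.9% at D = 0, through 81/120 = 67.5% at D = 20, to 81/106 = 76.4% at D = 34. Against the upper end, the marker rates differ by 80.0 − 76.4 = +3.6 points (lactate), 93.6 − 76.4 = +17.2 (CPO) and 74.0 − 76.4 = −2.4 (PAPi). Against the printed 57.9% the gaps are +22.1, +35.7 and +16.1.

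If nobody was unmeasured, not-met survival for D from 0 to 34 would run from 9/50 = 18% to 9/16 = 56% (lactate), from 8/62 = 13% to 8/28 = 29% (CPO), and from 10/44 = 23% to 10/10 = 100% (PAPi). Unmeasured patients widen these ranges further.

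**Step 5: precision in 2018.** Exact 95% intervals are 74.9% to 99.1% for 24/26 (if that is the true count), 74.0% to 99.0% for 23/25, and 66.3% to 95.8% for 23/27. All three contain the overall 81.3%.

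**The case against.** The best defense is that the error is probably one wrong digit, that the results are labelled preliminary, and that the article lists the marker rates descriptively without offering them as the answer to the third objective. The Discussion does not mention the markers, and no test or sample size uses them. It is also true that the document does not say how early deaths or missing values were handled, and such detail is commonly left to an analysis plan. All of this stands. It limits the point to what the printed figures can support, but it does not make 24/36 possible or supply a comparator.

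Three stronger readings are tempting and not supported:
- A reader might infer that the marker rates are the only reported data on hemodynamic-guided management. They are not. The Results also give the right heart catheterization association, and the Introduction names early catheterization as a team goal serving invasive hemodynamic therapy. That result also lacks counts, an interval and a historical comparator, so it does not meet the objective either.
- A reader might infer that the misprint is why the third objective is unanswered. Correcting the denominator would leave that objective where it is; the missing comparator is the reason.
- A reader might suspect the lactate unit. The document gives no other lactate unit or threshold, so there is no internal contradiction to report.

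**Conclusion.** The 2018 lactate result is wrong as printed: 66.7% from its fraction against 92.3% stated, with 4 patients more than the cohort and 6 deaths more than occurred in it. The conflicts of percentage and cohort size need no assumption beyond the article's own 2018 total. The death count also assumes that marker survival and overall survival are the same outcome. 24/26 is the likely intended figure but remains an inference.

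Separately, the six marker rates describe team-era patients at target and cannot show an effect of reaching the targets. Depending on the unreported number of early deaths, the 2017 lactate and PAPi gaps over patients alive at 12 hours could be close to zero. The CPO gap would persist at 17 points or more, but as prognosis and not as an effect of care. These ranges assume that nobody who died before 12 hours was counted at target. The abstract's third objective, as distinct from the third specific aim, remains without its historical comparison for hemodynamic-guided management.

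**What to change.** 1. Check the 2018 lactate count against source data and correct the fraction or the percentage.
2. For each marker and year, restrict to patients alive with that marker measured at 12 hours. Report survival for met and not met, with the difference, its standard error and 95% CI, as the Method of Data Analysis section already promises. The at-target counts should not change; the gain is a proper not-met group.
3. State for each marker how many patients died before 12 hours and how many were unmeasured, and say what time the 12 hours are counted from.
4. Label the result as prognostic within the team era, and do not present it or the catheterization association as meeting the abstract's third objective. That objective needs a matching 2015-2016 group, or a statement that the comparison cannot be made.

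The cost is a data check and a re-tabulation, which the registry data should allow. The downside is smaller denominators and less striking contrasts, most of all in 2018, where only 5 to 7 patients lie outside each marker group (taking lactate as 24/26).

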#### Inclusion Criteria

Patients at the IHVI with documented Cardiogenic Shock team intervention for acute decompensated heart failure cardiogenic shock, or acute myocardial infarction cardiogenic shock.

Specific criteria for the diagnosis of cardiogenic shock is defined by hemodynamic parameters—systolic blood pressure <90 mm Hg, cardiac index <1.8 L/min/m^2^ without pharmacologic support (or >2.2 L/min/m^2^ with support), left ventricular end-diastolic pressure >18 mm Hg or right ventricular end-diastolic pressure >10-15 mm Hg or pulmonary capillary wedge pressure >15 mm Hg—and clinical signs and symptoms of hypoperfusion, such as cool extremities, decreased urine output, and altered mental status.

Enrollment criteria are specific to patients treated at the IHVI for documented cardiogenic shock with activation of the IHVI Cardiogenic Shock team. Cardiogenic shock will have preceded acute decompensated heart failure or acute myocardial infarction etiologies. Patients will include those transferred from offsite hospitals as well as inpatients at the IHVI.

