## Discussion

Retrospective clinical outcomes (acute decompensated heart failure cardiogenic shock, acute myocardial infarction cardiogenic shock) demonstrated an increase in current survival rates when compared to pre-Cardiogenic Shock team initiation. IHVI site specific positive outcomes far exceeded the national average. Patients who had mechanical circulatory support did significantly better when the patient was younger than 75 years old at the time of intervention and when the mechanical circulatory support was initiated within five hours of the patients’ arrival at the IHVI. Yet to be analyzed is the significance of the type of intervention ECMO versus intracorporeal axial-flow (Impella).

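### The time-to-MCS figures are printed as survival increases, which they cannot plausibly be, and no reported comparison supports the Discussion's five-hour statement

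*Protocol article*

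**What the plan says.** The Results section of the protocol article reports, as a preliminary finding: "Decreases of 5 and 10 hours in the time to implement MCS were associated with increased survival 53.6% and 135.8%, respectively". The sentence gives no effect measure, model, number of patients, confidence interval, P value or starting point for the time. The sentence after it reports age as an odds ratio with a 95% CI (3.43, 1.20 to 9.78).

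For context, the same section begins "Compared to a baseline 2016 survival rate of 47.0"% and continues "CS survival rates were increased to 57.9% (81/140) and 81.3% (26/32), respectively". Survival by etiology is 52.6% and 75.0% for acute myocardial infarction, and 61.4% and 87.5% for acute decompensated heart failure.

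The Discussion says that patients on MCS fared significantly better below age 75 and "when the mechanical circulatory support was initiated within five hours of the" patient's arrival at the institute.

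The section Method of Data Analysis promises standard errors and 95% confidence intervals for reported differences.

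**The concern.** Two printed statements are at issue.

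- **The effect size.** A reader will take the sentence at face value: MCS ten hours sooner more than doubles survival. With more than half of the 2017 patients surviving, there is no room for that. If the figures are ratios on another scale, the wording overstates the gain several-fold. The 10-hour figure may also look like extra evidence of a dose-response when it only restates the 5-hour figure.
- **The five-hour statement.** A difference of five hours between two patients is not the same as starting before hour five. The Discussion attaches statistical significance to the second, while the Results report only the first. A named time limit is the kind of conclusion that other centers may adopt.

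**Working it through.** **Inputs, all from the Results section.** Ratios implied by the text: 1.536 for 5 hours and 2.358 for 10 hours. Survival rates: 47.0% (2016); 81/140 = 57.9% (2017); 26/32 = 81.3% (2018); by etiology 30/57 = 52.6%, 12/16 = 75.0%, 51/83 = 61.4% and 14/16 = 87.5%.

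**1. Reproducing the 10-hour figure from the 5-hour figure.**
- Log-linear: 1.536² = 2.3593, or +135.9%. Rounding of 53.6% allows 1.5355² = 2.3578 to 1.5365² = 2.3608, or +135.8% to +136.1%. The printed 135.8% is reproduced.
- Additive: 2 × 53.6 = 107.2%. This does not reproduce it.
- Slope per hour: ln(1.536)/5 = 0.0858 and ln(2.358)/10 = 0.0858. The two figures are one slope.

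**2. Can the figures be increases in survival?**
- As percentage points: a gain of 135.8 points is impossible from any starting value.
- As a relative rise: p × 2.358 ≤ 1 requires p ≤ 1/2.358 = 42.4%. The 5-hour figure alone requires only p ≤ 1/1.536 = 65.1%, so the 10-hour figure is the one that gives the problem away.
- Survival for a 10-hour decrease under the literal reading:

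| Reference survival | × 2.358 |
|---|---|
| 47.0% | 110.8% |
| 52.6% | 124.1% |
| 57.9% | 136.4% |
| 61.4% | 144.9% |
| 81.3% | 191.6% |

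The remaining two rates, 75.0% and 87.5%, also exceed 42.4%.

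**3. What the figures would mean as odds ratios.** Formula: new odds = p/(1 − p) × OR; new survival = new odds/(1 + new odds).
- Assumed reference 57.9%: odds 81/59 = 1.373.
  - 5 hours: 1.373 × 1.536 = 2.109, survival 67.8% (+10.0 points, 17.2% relative).
  - 10 hours: 1.373 × 2.358 = 3.237, survival 76.4% (+18.5 points, 32.0% relative).
- Assumed reference 47.0%: 57.7% for 5 hours and 67.6% for 10 hours.
- Assumed references from 30% to 81%: about +6 to +11 points for 5 hours and +10 to +21 points for 10 hours.
- Overstatement at 57.9% if the printed figures are read as relative survival: 53.6/17.2 = 3.1-fold and 135.8/32.0 = 4.2-fold.

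**4. The five-hour statement.** Under a constant slope, moving from 20 to 15 hours carries the same ratio as moving from 7 to 2 hours. Such a slope has no special point at five hours. The Results contain no comparison of patients supported before and after five hours and no cut-point analysis.

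**The case against.** **The effect measure is not stated.** Squaring shows a log-linear slope and nothing more; an inverse hazard ratio or a log-link risk ratio would square in the same way. This stands. A reader might take it as established that these are odds ratios. The binary outcome and the age odds ratio in the next sentence make that the likely reading, but the text does not settle it.

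**The reference group is not reported.** The 57.9% covers all 2017 patients, not MCS recipients treated ten hours later. A late-treated group with survival of at most 42.4% would make the literal reading possible. This also stands, so the right word for the relative reading is implausible. Only the percentage-point reading is impossible.

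**Two increments of one variable are ordinary presentation.** Agreed. The article does not call them separate evidence; a short note that they share a slope is enough.

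**A five-hour analysis may exist unreported.** It may, just as the age cut-off in the same Discussion sentence has a reported odds ratio behind it. A reader might infer that the 5-hour increment was turned into a threshold, but the article does not show where the statement came from. What can be said is that nothing reported supports it.

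**Broader bias charges.** A reader might go on to infer that the aim to compare "outcomes related to implementation of mechanical circulatory support versus no circulatory intervention" suffers from immortal time. The Specific Aims fix no rule for classifying patients who die before placement, and that rule may sit in the full protocol or analysis plan. Likewise, "Patients will include those transferred from offsite hospitals as well as inpatients at the IHVI" does not say that transferred patients arrived already on support. Survivor selection among MCS recipients could also work against the reported association, because those treated late had to live longer to be treated. These charges are not part of the point.

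**Conclusion.** The point holds as a reporting error with a consequence for interpretation. The printed figures cannot plausibly be increases in survival at any overall or etiology-specific rate that the article gives, and they amount to one slope of about 0.086 per hour on a log scale. If they are odds ratios and the reference is 57.9%, the absolute gains are about 10 and 18.5 points, and the printed wording overstates the relative gain roughly three- to four-fold. Both conditions are assumptions. The precision of the slope is unknown: no interval, P value or number of patients is shown, although the article promises intervals for reported differences and gives one for age.

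The claim of significance within five hours of arrival has no reported comparison behind it and does not follow from the slope. An unseen analysis plan would not cure either matter, because both are printed results or conclusions. None of this bears on when MCS should be given.

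**What to change.** - Name the model and the effect measure for time to MCS.
- Report one ratio per 5 hours (if confirmed, an odds ratio for survival of about 1.54) with the number of patients, the 95% CI and the absolute survival it implies from a stated reference.
- Say that the 10-hour figure is the same slope, or leave it out.
- State the time origin. The Results give none, and arrival is mentioned only in the Discussion.
- Either report the analysis behind the five-hour statement, with its groups, counts and interval, or remove the statement.

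The cost is small: re-wording of two sentences and output from a model that has evidently been fitted. Only a five-hour comparison, if none has been run and the authors wish to keep the statement, would need new analysis.
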